**Discussion:**

This trial aims to provide robust clinical evidence for the integration of MSNP into the management of postoperative mild-to-moderate depression in patients with NSCLC. Furthermore, multi-omics analyses are expected to elucidate the multi-target and multi-pathway mechanisms of MSNP, offering insights into personalized and integrative therapeutic strategies.

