#### Primary outcome

2.6.1

The primary outcome of this trial is the total effective rate at the end of the 6-week treatment period, defined as the proportion of participants achieving a ≥25% reduction in their HAMD-17 total score from baseline (Wang et al., 2019). The HAMD-17 is an observer-rated instrument designed to assess depressive symptoms in individuals with a clinical diagnosis of depression. According to standard thresholds, a HAMD-17 score of 0–7 indicates no depression, 8–16 indicates mild depression, 17–23 indicates moderate depression, and ≥24 indicates severe depression (Zimmerman et al., 2013). Treatment response is categorized into four groups based on the percentage reduction in HAMD-17 scores from baseline: recovery (≥75% reduction), markedly effective (≥50% reduction), improved (≥25% reduction), and ineffective (<25% reduction) (Wang et al., 2019). The total effective rate is defined as the proportion of participants classified as recovered, markedly effective, or improved.

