#### Secondary outcomes

2.6.2

Change from baseline in HAMD-17 total scores. Assessments will be performed at baseline, during the treatment phase (Weeks 2, 4, and 6), and at the Week 10 follow-up visit.Depression remission rate at the end of the 6-week treatment period, defined as the proportion of participants achieving a HAMD-17 total score of ≤7 (Zhao et al., 2019).Change from baseline in Patient Health Questionnaire-9 (PHQ-9) total scores. The PHQ-9 is a self-administered tool used to assess the severity of depressive symptoms over the past 2 weeks. It consists of 9 items, each scored from 0 to 3, with total scores ranging from 0 to 27. Scores of 0–4 are considered normal; 5–9 indicate mild depression; 10–14, moderate depression; 15–19, moderately severe depression; and 20–27, severe depression (Sun et al., 2020). Assessments will be conducted at baseline and at Weeks 2, 4, 6, and 10.Proportion of participants requiring an increased dosage of paroxetine during the 6-week treatment period.Change from baseline in Generalized Anxiety Disorder-7 (GAD-7) total scores. The GAD-7 is a self-reported screening and assessment tool for anxiety symptoms over the past 2 weeks. It consists of 7 items scored from 0 to 3, with total scores ranging from 0 to 21. Higher scores indicate greater anxiety severity, with a score ≥10 is generally considered clinically significant (Aktürk et al., 2025). Assessments will be performed at baseline, and at Weeks 2, 4, 6, and 10.Change from baseline in Pittsburgh Sleep Quality Index (PSQI) total scores. The PSQI assesses sleep quality over the past month across seven domains, each scored from 0 to 3, with total scores ranging from 0 to 21. Scores of 0–5 indicate very good sleep quality; 6–10, good; 11–15, average; and >15, poor sleep quality (Wang et al., 2024). Assessments will be performed at baseline, and at Weeks 6 and 10.Change from baseline in Functional Assessment of Cancer Therapy–Lung (FACT-L) total scores. The FACT-L is a validated instrument assessing health-related quality of life in patients with lung cancer. It consists of 36 items scored from 0 to 4, with total scores ranging from 0 to 144. The scale includes a general cancer subscale (27 items) and a lung cancer-specific subscale (9 items) (Cella et al., 1995). Higher scores indicate better quality of life. Assessments will be performed at baseline, and at Weeks 6 and 10.Change from baseline in Fear of Cancer Recurrence Inventory–Severity Subscale (FCRI-S) total scores. The FCRI-S assesses the severity of fear of cancer recurrence over the past month (Savard et al., 2023). It consists of 9 items scored from 0 to 4, with total scores ranging from 0 to 36. Higher scores indicate greater fear of cancer recurrence severity, with a score ≥13 generally considered clinically significant (Simard and Savard, 2015). Assessments will be performed at baseline, and at Weeks 6 and 10.Progression-free survival (PFS) and OS in patients with lung cancer. PFS is defined as the time from randomization to the first documented disease progression, based on the Response Evaluation Criteria in Solid Tumors (RECIST) version 1.1 (Bogaerts et al., 2009), or death from any cause, whichever occurs first. OS is defined as the time from randomization to death from any cause.

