
#### Exploratory outcomes

2.6.3

To systematically investigate the potential mechanisms of action of MSNP granules, biological samples will be collected for analysis. At each study center, the first 20 participants enrolled in each stratification group (with or without concomitant paroxetine use) will be selected, yielding a total of 40 participants per center for mechanistic assessments. Peripheral blood and fecal samples will be obtained at baseline and at Week 6. Fasting venous blood samples will be drawn from the antecubital vein between 8:00 and 10:00 a.m. After standing at room temperature for 1 h, the samples will be centrifuged at 3,000 rpm for 1 min to obtain the supernatant. This will be followed by a second centrifugation at 12,000 rpm for 10 min at 4 °C to isolate serum (Wang et al., 2022). Fecal samples will be collected immediately after morning defecation using sterile containers. All serum and fecal specimens will be stored at −80 °C until further analysis. The following mechanistic indicators will be assessed:Serum inflammatory markers, including interleukin-1β (IL-1β), interleukin-6 (IL-6), C-reactive protein (CRP), and tumor necrosis factor-α (TNF-α), measured using enzyme-linked immunosorbent assay (ELISA).Serum hormones associated with the HPA axis, including adrenocorticotropic hormone (ACTH), corticotropin-releasing hormone (CRH), and cortisol (CORT), also measured using ELISA.Serum neurotransmitters, including dopamine (DA), norepinephrine (NE), and 5-hydroxytryptamine (5-HT), quantified using high-performance liquid chromatography with electrochemical detection.Serum BDNF, measured using ELISA.Serum metabolomic profiles, analyzed through non-targeted liquid chromatography–mass spectrometry.Gut microbiota composition, assessed via 16S rRNA gene sequencing.

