### Statistical analysis

2.14

All efficacy analyses will be performed according to the intention-to-treat (ITT) principle in all randomized participants. Safety analyses will be conducted in all participants who initiate protocol-defined treatment. Missing outcome data will be handled using multiple imputation under the missing-at-random assumption.

The primary outcome (total effective rate) will be analyzed using a log-binomial regression model to estimate the adjusted RR and corresponding 95% confidence interval (CI) between the intervention and control groups. The model will include study center and concomitant paroxetine use as covariates. An interaction term between treatment group and paroxetine use will be included to assess the potential moderating effect of antidepressant co-administration on the intervention effect. Sensitivity analyses will include a predefined per-protocol (PP) analysis to assess the robustness of the findings. The PP population will include participants who complete the entire treatment course without major protocol violations and have available primary outcome data. Prespecified subgroup analyses will be performed according to baseline sex (male vs. female), age (≤55 vs. >55 years), depression severity (mild vs. moderate), NSCLC stage (I vs. II vs. III), and KPS score (70–80 vs. 90–100).

For other outcomes, repeated-measures continuous variables such as HAMD-17, PHQ-9, and GAD-7 scores will be analyzed using linear mixed-effects models to evaluate longitudinal changes from baseline between groups. The models will include group, time, group-by-time interaction, and baseline score as fixed effects, and participant and study center as random effects. For single-timepoint continuous variables such as inflammatory markers and neurotransmitters, between-group comparisons will be conducted using independent-samples t-tests or Mann–Whitney U tests, depending on data distribution. For time-to-event outcomes including PFS and OS, Cox proportional hazards models will be used to estimate hazard ratios and 95% CIs, adjusting for study center and paroxetine use. For categorical outcomes such as AE incidence and depression remission rate, group comparisons will be conducted using the chi-square test or Fisher’s exact test, as appropriate.

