Several potential limitations should be noted. First, the study does not include a head-to-head comparison between MSNP and standard antidepressants. If the results are promising, future trials may consider such comparative studies. Second, this trial focuses on patients with postoperative depression after NSCLC surgery. Future studies could expand to include other cancer types or general depressive populations to further examine the generalizability and clinical applicability of MSNP. Third, current mechanistic investigations are primarily based on peripheral biomarkers. Future research may incorporate neuroimaging techniques, such as functional magnetic resonance imaging and positron emission tomography, to assess MSNP’s impact on brain network activity and further elucidate its central mechanisms of action.

In summary, by integrating a rigorously designed randomized controlled trial with systematic omics-based analyses, this study aims to construct a coherent evidence chain linking clinical efficacy with biological mechanisms. The findings are expected to support the clinical application of MSNP in the treatment of postoperative mild-to-moderate depression in NSCLC patients and contribute to the modernization and translational development of TCM interventions for cancer-related psychological disorders.

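### The stated biomarker test (unadjusted, between arms) cannot link efficacy to mechanism; the samples allow an association with response to be shown, but not its direction

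*Protocol article*

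**What the plan says.** **Aim.** The closing paragraph of the Discussion states an aim to "construct a coherent evidence chain linking clinical efficacy with biological mechanisms". The Discussion paragraph of the Abstract says that "multi-omics analyses are expected to elucidate the multi-target and multi-pathway mechanisms of MSNP". Section 2.6.3 is more cautious. It lists the markers as exploratory outcomes and opens: "To systematically investigate the potential mechanisms of action of MSNP granules, biological samples will be collected for analysis".

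**Sampling.** Section 2.6.3: "Peripheral blood and fecal samples will be obtained at baseline and at Week 6". The subset is the first 20 participants in each paroxetine stratum at each of nine centers.

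**Clinical outcome.** Section 2.6.1: "The primary outcome of this trial is the total effective rate at the end of the 6-week treatment period". Section 2.6.2 has HAMD-17 rated at baseline, "during the treatment phase (Weeks 2, 4, and 6), and at the Week 10 follow-up visit".

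**Analysis.** Section 2.14: "For single-timepoint continuous variables such as inflammatory markers and neurotransmitters", "between-group comparisons will be conducted using independent-samples t-tests" or Mann-Whitney U tests. No baseline value, stratum or center enters this comparison. Nothing in the article relates a marker to HAMD-17 in the same participant.

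**The concern.** A link between efficacy and mechanism is a statement about participants: those whose marker moved are those whose mood improved. A test between arms answers a different question, namely whether MSNP shifts the average marker level. It gives a positive result whether the marker causes the improvement, results from it, or has nothing to do with it.

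Timing adds a second limit. The one on-treatment sample coincides with the primary outcome, so even a clear association leaves open which change came first.

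The description of the markers as single-timepoint also conflicts with the two sampling times, and the named test leaves the baseline value unused. If section 2.14 is followed as written, a list of arm differences is all there is to support a mechanistic conclusion, although paired marker and HAMD-17 data exist for the same people.

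**Working it through.** **The plan's own figures.** The article calculates no size for the mechanistic analysis. Its only calculated size is for the primary outcome and is not in dispute. Pooled-variance formula, two-sided 0.05, 80% power, then division by 0.85:
- 59.6% vs 37.0%: 76 per arm, 90 after dropout, 180 in total (stated 180).
- 91.6% vs 79.0%: 123 per arm, 145 after dropout, 290 in total (stated 288; power at 288 with 15% dropout is 79.9%).

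**Subset (section 2.6.3).** 9 centers × 40 = 360, so about 180 per arm. With the plan's 15% dropout, 306 remain, or 153 per arm.

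**Can the stated test separate the explanations?** Let T be arm (0/1), M the marker, Y improvement in mood, and e independent standard normal errors. The coefficients are assumptions for illustration.
- (a) Marker drives mood: M = 0.5T + e; Y = 0.6M + 0.2T + 0.8e.
- (b) Mood drives marker: Y = 0.5T + e; M = 0.6Y + 0.2T + 0.8e.
- (c) No link: M = 0.5T + e; Y = 0.5T + e.

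In each case the arm difference in M is 0.5. The within-arm variance of M is 1 (in (b), 0.36 + 0.64), and the arms add 0.5² × 0.25 = 0.0625. The standardized difference is therefore 0.5/√1.0625 = 0.485 in all three. At 153 to 180 per arm the planned test is significant in about 99% or more of trials under each of them.

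**What a within-participant model adds.** The within-arm correlation of M and Y is 0.6 in (a), 0.6 in (b) and 0 in (c). Regressing Y on T and M:
- In (c), M is flagged in about 5% of simulated trials, the nominal rate. In (a) and (b) it is flagged in essentially all. The model separates linked from unlinked markers.
- In (a) and (b) the coefficient on M is 0.6, so the apparent indirect effect is 0.5 × 0.6 = 0.30 in both. The model does not separate cause from consequence.

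**Precision for one marker, no multiplicity adjustment, 80% power.** The smallest detectable correlation is tanh[(1.960 + 0.842)/√(n − 3)]:
- n = 360: 0.147; n = 306: 0.160.
- Within one stratum, n = 180: 0.208; n = 153: 0.225.

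The planned arm comparison detects √(2/n) × 2.802, which is 0.30 SD at 180 per arm and 0.32 SD at 153.

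**How often would a marker that only follows mood differ between arms?** On a normal latent scale the planning rates imply z(0.596) − z(0.370) = 0.575 and z(0.916) − z(0.790) = 0.572. Assume a HAMD-17 effect of 0.5 to 0.575 SD and a marker-mood correlation of 0.3 to 0.5. The marker's arm difference is the product, 0.15 to 0.29 SD. The test is then significant in 26% of trials (153 per arm, 0.15) to 78% (180 per arm, 0.29).

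**Multiplicity.** The named markers number 4 inflammatory + 3 HPA + 3 neurotransmitter + 1 BDNF = 11. If all were null and independent, the chance of at least one p ≤ 0.05 is 1 − 0.95¹¹ = 43%.

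**Does Week 10 HAMD-17 settle direction?** It is the only rating after the Week 6 sample. Simulate a non-causal marker that follows mood (correlation 0.3 to 0.5, n = 306 to 360), with assumed HAMD-17 reliability of 0.8 to 0.9 and a Week 6 to Week 10 mood correlation of 0.7. A model of Week 10 HAMD-17 given Week 6 HAMD-17 flags the marker in about 7% to 47% of trials instead of 5%. Adjusting for an imperfectly measured mood score leaves residual confounding by mood.

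**The case against.** The best defense is that this is an exploratory component. The strong wording sits in the Abstract and Discussion, while section 2.6.3 speaks of potential mechanisms, and no efficacy or safety conclusion depends on it. An association or mediation model may also be in an analysis plan that is not shown, so its absence from an article is not in itself an error. Both points stand, and they limit the weight of the concern. They do not remove it, because the article is not silent: it names a specific test for these markers, classes them in a way that conflicts with its own sampling, and fixes the sampling times.

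A reader might infer that no link can be shown at all. The documents do not support that. Markers and HAMD-17 are both measured at baseline and Week 6 in up to 360 participants, so an association can be estimated well; same-visit sampling blocks only its direction.

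A reader might also take the 26% to 78% as an error rate of the planned test. It is not. In that scenario MSNP truly shifts the marker by way of mood, and the test correctly reports it; the error would lie in calling it a mechanism. The 43% is a separate multiplicity point, and related cytokines or hormones are unlikely to be independent.

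Finally, a within-participant model will itself nearly always flag a marker that merely follows mood. That is true, and it is why the wording must change as well as the model.

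**Conclusion.** The concern holds in a limited form. The stated between-arm test cannot support the aim of linking efficacy with mechanism, since three different causal structures give the same arm difference (0.485 SD in the illustration). With the only on-treatment sample at the primary-outcome visit, the trial can show an association with response (correlations of about 0.15 to 0.16 are detectable in the full subset) but not that marker change precedes or mediates the Week 6 effect.

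The argument that the arm comparison is uninformative about linkage does not depend on the chosen coefficients; the particular effect sizes, correlations and reliabilities are assumptions. The outcomes are exploratory, so this should be corrected but does not threaten the trial's main conclusions.

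**What to change.** In section 2.14, labelled exploratory and confined to the mechanistic subset:
1. Compare each Week 6 marker between arms adjusted for its baseline value, paroxetine stratum and center, and drop the single-timepoint description.
2. Add a within-participant model of Week 6 HAMD-17 on arm, stratum, center, baseline HAMD-17, baseline marker and Week 6 marker. State that it separates linked from unlinked markers and does not establish direction.
3. Control the false discovery rate across the 11 named markers.
4. In the Abstract and the closing paragraph of the Discussion, describe the expected product as arm differences and associations, with direction not established.

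Do not offer a model of Week 10 HAMD-17 given Week 6 HAMD-17 as evidence of direction.

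Cost: slightly more analysis and some rewording, with no new samples, visits or participants. The downside is a weaker mechanistic claim than the article now advertises.
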